### Endpoints

#### Primary endpoint

Cervical infection with HPV-16 and/or HPV-18 (by PCR), *defined as at least one positive HPV-16 or HPV-18 DNA PCR assay at enrollment (Month 0) or follow-up (Month 36) or any additional screenings during the study period.*

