### Aims

The study aims to evaluate the impact of the AS04 adjuvanted HPV 16/18 vaccine (Brand name: *Cervarix),* for HPV infection and related cervical diseases in real world, with the following objectives:To describe the incidence of HPV 16/18 infection by exposure status, and to evaluate the effectiveness of *Cervarix* on HPV 16/18 infection in birth cohortsTo describe the incidence of cervical lesions or diseases, and other 12 high-risk HPV infection by exposure status in birth cohorts

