### Exclusion criteria

The following criteria should be checked at the time of study entry. If any apply, the subjects must not be included in the study:Pregnancy at the enrollment.Females with historical cervical diseases (i.e., cervical intraepithelial neoplasia (CIN)1, CIN2, CIN3, and cervical cancer) before the recruitment.After hysterectomy.Females with malignant tumor history or other severe diseases (e.g., liver failure, heart failure, etc.), whose life expectancy is less than 12 months.Females who (1) have historical HPV vaccination, or (2) are in non-exposed groups but have clear intention for HPV vaccination in next 3 years (confirmed by field investigators before enrollment).Any high-risk HPV (hr-HPV) DNA (i.e., HPV 16/18/*31/33/35/39/45/51/52/56/58/59/66/68*) positive result at baseline.Having abnormal colposcope diagnosis or cervical diseases at the baseline screening (women tested HPV positive or having abnormal colposcope diagnosis or cervical disease will be followed up and managed through the local referral system).

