### Sample size

Per the previous research, the effectiveness assumptions for *Cervarix* will be 83%, 66%, and 50% for the cohorts of 9–20, 21–30 and 31–45 years of age respectively [23, 24]. The frequency of exposed group vs. non-exposed group will equal to 1: 1 with the level of significance α = 0.05 and statistic power 1-β = 0.8. The statistical analysis was performed on PASS15.0 (Tests for Two Proportions). Considering the loss to follow-up (5% estimated) and subtraction due to the baseline HPV infection and the contamination during follow-up (25% estimated), there will be 30% loss at the end of study. To mitigate this, the targeting recruitment number will be 1/(1–0.3)*100% of the sample size of effectiveness calculation. The detailed variables and calculation of the sample size is demonstrated in the table below (Table 1).

**Table 1 Tab1:** Sample size calculation

Age group(y/o)	Incidence of HPV 16/18 infection	Vaccine effectiveness	Frequency ratio	Exposure group	Non-exposure group	Sample size for effectiveness calculation	Targeting recruitment number
9–20	0.02	0.83	1:1	661	661	1322	1890
21–30	0.02	0.66	1:1	1208	1208	2416	3452
31–45	0.02	0.50	1:1	2371	2371	4742	6776
Total	-	-	-	4240	4240	8480	12,118

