#### Secondary endpoints

Cervical infection with HPV-16 and/or HPV-18 over 12 months (measured by two tests with an interval of 12 months), *defined as at least one positive HPV-16 or HPV-18 DNA PCR assay at the additional visit in 12 months after getting the positive HPV-16 or HPV-18 test result at enrollment (Month 0) or follow-up (Month 36) or any additional screenings during the study period.*

Cervical infection with 12 other high-risk HPV besides of type 16/18 (by PCR), *defined as at least one positive for HPV 31/33/35/39/45/51/52/56/58/59/66/68 or multiple types DNA PCR assay at enrollment (Month 0) or follow-up (Month 36) or any additional screenings during the study period.*

Any cervical lesions or diseases in birth cohorts, *defined as atypical squamous cells of undefined significance (ASC-US), atypical glandular cells (AGC), atypical squamous cells, cannot exclude for highly squamous intraepithelial lesions (ASC-H), low-grade squamous intraepithelial lesion (LSIL), high-grade squamous intraepithelial lesion (HSIL), Cervical Intraepithelial Neoplasia (CIN) 1, CIN2, CIN3, squamous cell carcinoma (SCC), adenocarcinoma *in situ* (AIS) and adenocarcinoma (ADC). Any hr-HPV type infection is defined as at least one positive for HPV 16/18/31/33/35/39/45/51/52/56/58/59/66/68 or multiple types DNA PCR assay in the aforesaid cervical sample.*

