**Fig. 2 Fig2:**
[figure not shown]
Study procedure

Subjects will be stratified into three age groups (9–20 y/o, 21–30 y/o and 31–45 y/o) and divided into exposed and non-exposed groups by vaccination status. The exposed group will include subjects who received 1 or 2 doses of *Cervarix* and the non-exposed group will include subjects who did not receive any doses of HPV vaccine.

During the study period, two visits will be scheduled for all subjects at Month 0 and Month 36, which means the follow-up period will be 3 years. In the first visit, the questionnaire survey will be administrated for all the subjects to obtain the demographic information, sexual history, menstrual and obstetrical histories, etc. For the ones who are eligible for the cervical cancer screening (i, Have sexual debut at the enrollment; ii, no contradiction of screening and iii, are willing to undergo the screening), the type-specific HPV DNA PCR testing will be given within 2 weeks after the enrollment. After 3-years follow-up, the subjects will be called back for the second visit. A questionnaire which measures any changes of behavior during the follow-up period will be performed. Then the second screening with type-specific HPV DNA PCR testing will be given within 2 weeks after the call-back.

At each visit, type-specific HPV DNA PCR testing will be the primary screening approach, and for the ones with unsatisfactory findings (i.e., hr-HPV infection) will be referred to the local abnormal cervical cancer screening results management system for further medical activities (Fig. 1)

By the end of the follow-up period, the prevalence of the HPV infection, cervical disease (e.g., CIN1, CIN2, CIN3, SCC, AIS, etc.) will be described in each birth cohort by their exposure status. If the sample size is sufficient, the effectiveness of *Cervarix* will be assessed as the exploratory objective.

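### The primary endpoint and two secondary infection endpoints count Month 0 positivity as an event, contradicting the baseline HPV exclusion; if applied literally to women already enrolled, effectiveness is biased

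*Protocol article*

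**What the plan says.** The protocol article, Primary endpoint, gives this event definition: "at least one positive HPV-16 or HPV-18 DNA PCR assay at enrollment (Month 0) or follow-up (Month 36"). A positive result at an additional screening also counts. Under Secondary endpoints, the endpoint for the 12 other high-risk types uses the same time points ("or multiple types DNA PCR assay at enrollment (Month 0) or follow-up (Month 36")), and the endpoint for infection lasting over 12 months may start from a positive test at enrolment.

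Four other places treat baseline infection differently:

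- **Exclusion criteria.** "Any high-risk HPV (hr-HPV) DNA" positivity at baseline, with types 16 and 18 in the list, is a reason not to include a woman. The last criterion adds that "women tested HPV positive or having abnormal colposcope diagnosis or cervical disease will be followed up and managed through the local referral system".
- **Sample size.** The allowance for losses includes "subtraction due to the baseline HPV infection and the contamination during follow-up (25% estimated").
- **Aims.** The first objective is "To describe the incidence of HPV 16/18 infection by exposure status" and to evaluate effectiveness against it.
- **Study procedure (text after Fig. 2).** For women eligible for screening, "the type-specific HPV DNA PCR testing will be given within 2 weeks after the enrollment". Eligibility for screening requires sexual debut, no contraindication and willingness.

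The Drop-out criteria do not mention a positive baseline HPV test.

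**The concern.** An infection found at Month 0 was not acquired during follow-up, so it is not an incident case and says nothing about protection after vaccination. The exclusion and the sample size remove such a woman, while the endpoint definition makes her a case.

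The timing gives the conflict practical weight. Exclusions are to be checked at study entry, but the PCR result can arrive after enrolment. Some baseline-positive women will then already be in the cohort, and the article's withdrawal rules do not take them out. An analyst who follows the endpoint text counts them; one who follows the exclusion and the sample-size text removes them. With an assumed incidence of only 2%, even a small number of Month 0 positives would noticeably change the primary estimate.

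**Working it through.** **1. The plan's own figures.** Inputs from Sample size and Table 1: incidence 0.02 in unexposed women, effectiveness (VE) 0.83/0.66/0.50 for ages 9–20/21–30/31–45, α = 0.05 (taken as two-sided), power 0.80, ratio 1:1.

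With p1 = 0.02, p2 = 0.02 × (1 − VE) = 0.0034/0.0068/0.0100 and p̄ their mean, the pooled two-proportion formula is

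n per group = [1.96·√(2p̄(1−p̄)) + 0.8416·√(p1(1−p1) + p2(1−p2))]² / (p1 − p2)².

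It gives 658/1190/2319, against 661/1208/2371 stated (0.5%, 1.5% and 2.2% apart). Dividing the stated n by 0.7, rounding up and doubling gives 1890/3452/6776, total 12,118, exactly as in Table 1. The table is thus built on new infections at 2%, with baseline infection inside the 30% loss.

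**2. Exclusion enforced.** No analysed woman has a positive Month 0 test, so the clause adds no events. VE stays at 83/66/50% and power at the stated n is 0.802/0.806/0.809.

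**3. Endpoint applied literally, equal prevalence.** Let π be the proportion of all analysed women who are HPV 16/18 positive at Month 0. The article gives no value, so π is an assumption shown over a range.

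Risk, unexposed = π + (1 − π) × 0.02

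Risk, exposed = π + (1 − π) × 0.02 × (1 − VE)

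Apparent VE = 1 − risk exposed / risk unexposed, the 1 − relative risk measure named under Statistical analysis.

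Example, ages 9–20, π = 1%: unexposed 0.01 + 0.99 × 0.02 = 0.0298; exposed 0.01 + 0.99 × 0.0034 = 0.0134; apparent VE = 55%.

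| π in both groups | Apparent VE, 9–20 / 21–30 / 31–45 | Power at stated n |
|---|---|---|
| 0 | 83 / 66 / 50% | 0.802 / 0.806 / 0.809 |
| 0.5% | 66 / 53 / 40% | 0.651 / 0.672 / 0.689 |
| 1% | 55 / 44 / 33% | 0.538 / 0.568 / 0.591 |
| 2% | 41 / 33 / 25% | 0.395 / 0.427 / 0.454 |
| 3% | 33 / 26 / 20% | 0.312 / 0.341 / 0.366 |
| 5% | 23 / 18 / 14% | 0.223 / 0.245 / 0.266 |

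Women not tested at Month 0 cannot contribute a Month 0 event, so π equals the prevalence among tested women times the fraction tested. For example, 2% among tested women with half of the cohort tested gives π = 1%.

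**4. Endpoint applied literally, unequal prevalence (ages 31–45, planned VE 50%).** The prevalences are again assumed.

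- Exposed 0.2%, unexposed 2%: risks 0.002 + 0.998 × 0.01 = 0.0120 and 0.02 + 0.98 × 0.02 = 0.0396; apparent VE about 70%.
- Exposed 1%, unexposed 2%: risks 0.0199 and 0.0396; apparent VE about 50%, so the errors nearly cancel.
- Exposed 2%, unexposed 1%: both risks 0.0298; apparent VE 0%.

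**The case against.** The strongest reply is that the article shows what is intended. The exclusion, the referral of positive women, the planned subtraction of baseline infection and the incidence objective all point to removing Month 0 positives. Testing within two weeks of enrolment fits a plan to test first and subtract afterwards. On that reading the clause is surplus wording, and formal analysis sets may be left to a fuller document that is not shown.

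Much of this stands. A reader might infer that the exclusion and the endpoint cannot both be followed. That is too strong: with the exclusion enforced, the endpoint can be applied and its Month 0 part simply never fires. The estimates above are not a prediction either. They rest on an assumed prevalence, and those for ages 9–20 may be too pessimistic if many in that cohort are not tested at Month 0.

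The reply does not remove the point, for three reasons. The Month 0 wording stands in the primary endpoint and recurs in two secondary ones, and the 12-month endpoint actively uses an enrolment positive as its starting point, so this is not an isolated slip. Baseline-positive women are expected among those recruited, since the recruitment target is inflated for them. And no stated rule withdraws them once enrolled.

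**Conclusion.** The contradiction is real and sits in the definition of the primary event. Its effect on the result is conditional: none if the baseline exclusion is enforced; bias if the endpoint text is applied to women enrolled before their Month 0 result.

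A reader might infer that effectiveness would necessarily be pulled towards zero. The article does not support that. Dilution requires similar baseline prevalence in the two groups, and these groups are formed by vaccination status, not by randomisation. Under equal prevalence, an assumed 1% would take 83/66/50% to about 55/44/33%, and power from about 0.80 to between 0.54 and 0.59. Under unequal prevalence, the 50% for ages 31–45 could read anywhere from 0% to about 70% in the scenarios tried. All of these figures assume Table 1's 2% incidence and a prevalence that the article does not give. The same correction serves in every case.

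**What to change.** - Delete the reference to enrolment (Month 0) from the primary endpoint and from the two secondary infection endpoints.
- Define the primary event as a first HPV 16/18 positive after Month 0 in women not high-risk-HPV positive at Month 0. For the other 12 types, use a first positive for any of those types after Month 0 in the same women. Let the 12-month endpoint start only from a positive after Month 0.
- State that enrolled women whose Month 0 result is high-risk-HPV positive are removed from the effectiveness analysis, as the Exclusion criteria and Sample size sections imply.
- As a sensitivity analysis, analyse women tested negative at Month 0 separately from women not tested then. An untested woman may carry an infection from before enrolment that is later counted as new, and deleting the clause does not resolve this.
- Report Month 0 positivity by group as baseline prevalence.

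The cost is a change of wording, one sensitivity analysis and one descriptive table, with no new data collection. Table 1 needs no change: it is built on new infections, and its 25% allowance already includes baseline infection.

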**Methods:**

This is a prospective, multi-age birth cohort study to investigate the incidence and continuous status of HPV infection, and relevant cervical diseases by exposure status (with *Cervarix* vaccination history or without any HPV vaccination history). It is planned to recruit 12,118 eligible women at age of 9 to 45 years from vaccination clinics or hospital outpatient clinics, and then follow up them for three years. The standard questionnaire will be used to collect information such as demographic characteristics, menstruation and obstetrical histories, history of sexual behavior, personal behavior history, history of disease and pathogen infection, medication history, and family history at baseline. After three years, the changes of these behaviors will be investigated again, and other related health status information will be retrieved from the electronic health records during the follow-up period. If available physically and legally, the cervical cancer screening will be performed, including type-specific HPV deoxyribonucleic acid (DNA) polymerase chain reaction (PCR) testing and contingent thinprep cytologic test (TCT) and colposcopy. The free cervical cancer screening will be captured and uploaded timely to the Yinzhou Regional Health Information Platform (YRHIP); therefore, the long-term outcomes of participants will be monitored.

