## Background

Cervical cancer was the fourth most common cancer in women, with approximately 0.60 million cases and over 0.34 million deaths from cervical cancer worldwide in 2020 [1]. China is one of the countries with the most cases contributed with approximately 0.11 million cases and 0.05 million deaths [2]. Further, both the incidence of cervical cancer and disease burden still increased in the last decades, and its onset age becomes much younger in Chinese women [3, 4]. Human Papillomavirus (HPV) infection is the primary cause of cervical cancer [5], specifically, HPV16 and 18 infections accounted for 84.5% of invasive cervical cancer in China [6].

Expanding the coverage of HPV vaccines is an essential part of the 90–70-90 target proposed by the World Health Organization (WHO) for eliminating cervical cancer [7]. In a modeling study, with 70% coverage of bivalent vaccine, cancer cases can decrease by 58% to 33% in rural areas and 69% to 32% in urban areas at ages of 12 to 55, respectively [8]. China has also been making effort to increase vaccination coverage. Since 2016, HPV vaccines have been introduced for females aged 9–45 in mainland China, such as *Cervarix* (9–45 years old) in 2016, *Gardasil 4* (20–45 years old) in 2017, *Gardasil 9* (16–26 years old) in 2018 and the domestic bivalent HPV vaccine *Cecolin* (9–45 years old) in 2019 [9–12]. These vaccines were not included in the programmed immunization and were paid for by the receivers. Since 2020, some of cities in China have launched free HPV vaccination programs for girls under 14 years, which only included the domestic bivalent HPV vaccine *Cecolin* for now [13, 14]. In addition, China is also popularizing cervical cancer screening to accelerate the elimination of cervical cancer. China has initiated *the Two Cancers (the cervical cancer and breast cancer)* Screening Program in 2009, which provided females aged 35 years and over with cervical cancer and breast cancer screening for free [15]. Screening strategies varied across regions, including HPV-initiated and TCT-initiated tests. As for Yinzhou, Ningbo, where our study will be conducted, the standard cervical cancer screening process initiate with a type-specific HPV DNA PCR testing, and for the ones with HPV infection will be referred to colposcopy or cytology test, while those who are tested negative will be invited for another screening after 3 years (Fig. 1).

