### Data collection

All the data collected from the surveys and cervical cancer screenings will be documented in the YRHIP, (approval No.: GKYBSZ [2020] No. bc0015; Applicant: Ningbo Yinzhou Center for Disease Control and prevention; Approval time: October 2020).

Once the subject is recruited into the study with signed informed consent form, she will be identified in the YRHIP via her resident identification number and marked as the study subject, and new subpage which contains the study data will be created on her personal file in the YRHIP. The data of the paper-based questionnaire survey will be transcribed into corresponding fields and the cervical cancer screening data will be synchronized with existing healthcare activity page on real-time. Besides the survey and screening data, we’ll also obtain the data of general information, enrollment date, scheduled time of second visit, call-back status, HPV vaccination history, self-initiated cervical cancer screening, cervical related treatment or medication from the YRHIP.

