### Statistical analysis

We will describe the distribution and group differences of the subjects’ general characteristics and the incidence of HPV infection and relevant disease in each age cohort by the exposure status. The categorical data will be described by frequency (proportion) and the Chi-squared test will be performed to show the group difference. The continuous data will be described by mean (standard deviation), and non-normal distribution continuous data will be described by median (quantiles), and then the ANOVA or Wilcoxon rank-sum test will be performed to compare the difference across age groups. Also, the Kaplan–Meier method will be used to draw the survival graph, based on the actual number of cases of each endpoint.

The Logistic Regression will be performed to analyze the impact on HPV 16/18 infection, and HPV 31/33/45 infection in each birth cohort 3 years after vaccination, after adjusting the confounders such as the demographic characteristics, history of sexual behavior, personal behavior history, etc. The vaccine impact will be calculated by using (1-Relative Risk) and its 95% CI.

Stratification analysis will be conducted by frequency of sexual activity, numbers of sexual partners, extramarital sexual activity, family annual income, education level, and cervical cancer screen history. The interaction term between the above factors and HPV vaccination will be introduced into the Logistic regression model, and the differences between the model with interaction term and the model without interaction term will be compared, so as to evaluate the interaction between different factors and HPV vaccination.

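### The primary endpoint counts positives from unscheduled screening, so unequal testing of vaccinated and unvaccinated women would bias the effectiveness estimate

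*Protocol article*

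**What the plan says.** All references are to the protocol article.

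- **Primary endpoint.** A case is a woman with at least one positive HPV-16 or HPV-18 PCR at Month 0, at Month 36, "or any additional screenings during the study period".
- **Study procedure.** Only "two visits will be scheduled for all subjects at Month 0 and Month 36".
- **Data collection.** Besides study data, the investigators will obtain "self-initiated cervical cancer screening, cervical related treatment or medication from the YRHIP". The Methods part of the abstract adds that free programme screening is also captured on that platform.
- **Background.** The free national programme "provided females aged 35 years and over with cervical cancer and breast cancer screening for free". In Yinzhou a woman who tests negative is invited again after 3 years.
- **Statistical analysis.** The effect on HPV 16/18 infection at 3 years is estimated by logistic regression, adjusted for confounders such as demographics, sexual behaviour and personal behaviour. Stratified and interaction analyses include screening history. The Kaplan–Meier "method will be used to draw the survival graph, based on the actual number of cases of each endpoint".
- **Sample size, Table 1.** The column "Incidence of HPV 16/18 infection" is 0.02 in all three age groups. No time frame or number of tests is attached to it.

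**The concern.** HPV infection can be transient. With two scheduled tests 36 months apart, an infection acquired and cleared in between is invisible unless the woman happens to be tested while it is present. The endpoint therefore depends on how often she is tested as well as on whether she was infected.

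In a randomised trial one might hope that unscheduled testing balances out. Here exposure is self-selected: vaccinated women have chosen and usually paid for a vaccine, while unvaccinated women are enrolled only if they have no clear intention of being vaccinated in the next 3 years. Their screening habits may differ. If they do, the case counts differ without any vaccine effect, and this acts on the primary comparison.

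The survival graph raises a related problem. The only date this endpoint supplies is that of a positive test. Women tested only as scheduled can have an event only near Month 36, so any earlier step in the curve shows who was tested early. Onset is interval-censored.

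**Working it through.** **1. The plan's own figures.** Inputs from Sample size: 0.02 in the non-exposed, effectiveness 83%, 66% and 50%, α = 0.05 (taken as two-sided), power 0.80, 1:1, 30% loss. The pooled two-proportion formula is

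n = [z(0.975)·√(2p̄(1−p̄)) + z(0.80)·√(p₁(1−p₁)+p₂(1−p₂))]² / (p₁−p₂)²

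| Cohort | Computed n per group | Stated | Stated total / 0.7, rounded up | Stated target |
|---|---|---|---|---|
| 9–20 | 658 | 661 | 1322/0.7 → 1889 | 1890 |
| 21–30 | 1190 | 1208 | 2416/0.7 → 3452 | 3452 |
| 31–45 | 2319 | 2371 | 4742/0.7 → 6775 | 6776 |

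All agree within 3%, and the column totals are correct. The arithmetic of the sample size is not in question.

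**2. Detection by number of tests.** Assumptions, not in the documents: constant low incidence and exponential infection duration with mean D months, with g = 1/D.

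- Month 36 test only: detection is proportional to (1−e^(−36g))/g.
- Tests at Months 18 and 36: proportional to 2(1−e^(−18g))/g.
- Ratio r = 2(1−e^(−18g))/(1−e^(−36g)) = 2/(1+e^(−18g)).

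For D = 12: r = 2/(1+e^(−1.5)) = 2/1.2231 = 1.635. For D = 8 and D = 18, r = 1.81 and 1.46.

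**3. Effect on effectiveness.** Suppose the extra test is taken by 40% of one group and 20% of the other. These shares are also assumed.

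- More testing in the non-exposed: k = (1+0.2×0.635)/(1+0.4×0.635) = 1.127/1.254 = 0.899.
- More testing in the exposed: k = 1.254/1.127 = 1.113.
- Observed effectiveness = 1 − (1−VE)·k.

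| True VE | More tests in non-exposed | More tests in exposed |
|---|---|---|
| 0 | +10% | −11% |
| 50% | 55% | 44% |
| 66% | 69% | 62% |
| 83% | 85% | 81% |

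Over D = 18 to 8 months, a true effectiveness of 0 appears as +8% to +12%, or −8% to −14%.

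**4. A larger imbalance.** Take a two-state infection and clearance model set to 2% positive at Month 36 in the non-exposed, with D from 6 to 24 months and the Month 18 test taken by half of one group only. A true 50% is then observed as 57–65% (extra tests in the non-exposed) or 27–41% (in the exposed). A true 0 is observed as +15% to +31%, or −45% to −18%.

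**5. Where the extra tests can come from.** The free programme starts at 35. Women in the 9–20 and 21–30 cohorts are still under 35 at Month 36, so the programme reaches only the 31–45 cohort. A woman negative at baseline would next be invited at about Month 36. The irregular part is therefore mainly self-initiated testing.

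**The case against.** **What stands against the point.** No testing rate is given anywhere, so the 40%/20% split and the Month 18 test are invented for illustration. In that scenario the bias at the planned effects is modest. In the 31–45 cohort about 47 (2371 × 0.02) against 24 (2371 × 0.01) events are expected, and the 95% interval around an effectiveness of 50% is roughly 18% to 69%. A shift to 44% or 55% lies well inside it. The planned stratification by screening history is a partial safeguard, although it is not defined as tests during follow-up. The Kaplan–Meier curve is descriptive, the effect estimate comes from logistic regression, and event-time rules may sit in a fuller document. That the curve uses detection dates is an inference from the endpoint definition. Finally, a Month 36 endpoint measures infection present at that time and favours longer-lasting infections, while the first aim speaks of incidence.

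**Stronger readings that the documents do not support.**

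- A reader might infer that the bias can be neither known nor adjusted for. But the platform records the additional tests, so their number by group can be counted and partly adjusted for, and a Month 36 analysis can be run from the same data.
- A reader might infer that the non-exposed come from hospital clinics and are therefore screened more. The article names both vaccination sites and hospital clinics for participants in general and ties neither exposure group to a setting.
- A reader might infer that the study is underpowered, at about 33–36%. That requires the 2% to be 3-year cumulative true infection with a 12-month duration, so that Month 36 positivity is only 0.02 × (12/36) × (1−e^(−3)) = 0.63%. Sample size does not say this. The use of a test for two proportions, and the mention of prevalence at the end of follow-up, fit a detected proportion equally well.

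**Conclusion.** The point holds as a weakness in how the primary outcome is ascertained. The endpoint admits tests whose number and timing the protocol does not set, the comparison is not randomised, and no adjustment for tests during follow-up is described. Unequal testing would bias the effectiveness estimate in a direction that the documents do not show. The size depends on assumed infection duration and testing rates: about 5 to 6 percentage points at a true 50% in the moderate scenario, and up to about 23 points (50% observed as 27%) in the more extreme one. It is not shown that testing will differ, nor that any conclusion would be reversed. The sample size is sound if the 2% is positivity at Month 36. The change is worth making because it is cheap and best settled before follow-up data accrue.

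**What to change.** 1. Base the primary effectiveness comparison on the scheduled Month 36 PCR in women not HPV-positive at baseline, including those not yet eligible for a baseline test. This gives both groups the same ascertainment and fits the planned 3-year logistic regression.
2. Report the number of additional tests during follow-up by exposure group and age cohort.
3. Analyse detections from all tests as a supportive analysis that accounts for test count or uses interval-censored regression.
4. For the PCR endpoints, replace the Kaplan–Meier graph with an interval-censored estimate (Turnbull) or omit it.
5. State whether the 2% in Table 1 is Month 36 positivity or cumulative incidence. If it is Month 36 positivity, the stated sample size stands; if not, restate the power.

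Cost: changes of wording to the endpoint and analysis sections, with no new visit or data source. Infections detected only between visits leave the primary analysis, which then measures infection present at Month 36; they remain in the supportive analysis.
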